## Training interventions

Participants will be randomized to either NLPRT or RT of leg press, shoulder flexion, calf press and chest press exercises (three times per week for 8 weeks). The following will be similar for both the NLPRT and the RT groups.All exercises will be performed using training equipment available at each participating center. Leg press, chest press and calf press exercises will be performed using available weight machines and the shoulder flexion exercise will be performed using free weightsExercise order will be pre-determined: (1) leg press, (2) shoulder flexion, (3) calf press and (4) chest press. This exercise order will be used in order to alternate between lower and upper-limb exercises and between multiple- and single-joint exercises. All exercises will be performed bilaterallyRest between exercises will be standardized to 4 min and all exercises will be performed using dynamic repetitions with both concentric and eccentric muscle actions. The speed of motion in each exercise will be controlled by the breathing of the participant, we expect a moderate exercise velocity, i.e., 1–2:1–2 s in the concentric and the eccentric phase, respectivelyAll sessions will be supervised and conducted by local professionals using a group format, with approximately two to four participants per groupEach session will span approximately 60 min including a mandatory 5-min rest before and after the training sessions. During this time, oxygen saturation, heart rate, dyspnea and general fatigue (rated on the Borg revised category ratio 0–10 scale (Borg CR10) [23]), will be collectedDyspnea, limb-muscle fatigue and exertion ratings on Borg CR10, the later defined as “how heavy the exercise felt,” will be collected immediately after each set of exerciseExercise volume for each training session = (number of repetitions per set × sets per exercise × exercises per session) will be reportedNew 1 repetition max (RM) and multiple RM tests will be performed three times during the 8-week intervention period (after session 5, 10 and 15) in order to optimize exercise loadings. If a 1-RM test is lower than the prior 1 RM or if there is a mismatch between calculated training load from the new 1 RM and training load during the previous week, the higher training load will be used and a new test will be performed prior to the next training session to minimize the impact of alterations in daily fitnessNo general warm-up will be performed prior to sessions but a specific warm-up set of 15 repetitions using a load corresponding to 30% of 1RM prior to each exercises will be performed within the NLPRT and RT sessions

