##### Screening tests and baseline characteristics

A pulmonary function test (spirometry), while being on the participant’s usual bronchodilator therapy, will be obtained according to guidelines [28]. Anthropometrics will include height, weight and body mass index. To document baseline level of physical activity, participants will also be instructed to wear an accelerometer (DynaPort®, McRoberts BV, The Netherlands), placed on the lower back during seven consecutive days before the intervention period. The quantity of physical activity will be assessed using the median number of steps per day collected on at least two consecutive weekdays over at least 8 h of daytime [29]. Primary and secondary outcome assessments will be conducted at two (three if accepting a biopsy) test occasions at weeks 0 and 9 (before and after intervention). Before and directly after all physical tests, the perception of dyspnea and muscle fatigue will be measured with the Borg CR10 [23] as commonly and reliably used in patients with COPD [30–32].

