### Primary outcomes

#### Isotonic strength and endurance

Isotonic maximal strength (1 repetition maximum (1RM)) and endurance test (maximum number of repetitions performed at 45% of 1 RM) will be performed during leg press, shoulder flexion, calf press and chest press using a procedure earlier used in an untrained middle-aged population [33]. All RM tests will be separated by a 5-min rest period.

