All tests will be performed using exercise equipment that are available at each included center. Leg-press, chest-press and calf press tests will be performed using available weight machines and the shoulder flexion test will be performed using free weights. The tests will be performed in order to individualize progression and to determine the effects of the training performed after the 8-week intervention period. 1RM is defined as the maximum load able to be lifted with good technique through the full range of motion (ROM) [34]. The structure of all 1RM testing is designed so that a 1RM could be achieved in 3–5 attempts. All 1RM test will be preceded by a warm-up of 10 repetitions, using a light load, performed from the start position to the end position in each exercise. The start loading for 1RM testing will correspond to a perceived resistance of 50–70% of 1RM with gradual increases in each trial until 1RM is achieved. The rate of the gradual increase in load is dependent on the participant’s self-perceived capacity and 3–5 min of rest will be used between trials. Lastly, the settings and load of each exercise trial will be noted in the protocol.Leg press will be tested with the participants placed in a seated leg-press machine, adjusted so that the range of movement (ROM) of the knee joint will be from 90° flexion to full extension without discomfort in hip or ankle joints. Feet will be positioned shoulder-width apart and fully in contact with the surface during the whole ROM and arms held crossed over the chest. The start position for the test will be with the knee joint in 90° flexion. The placement of the feet will be noted so that the pre- and post-intervention testing will be done in the same positionShoulder flexion will be tested using dumbbells, performed while seated on a bench with backrest (120° hip angle) with both feet on the floor. Using one dumbbell in each hand, the participant starts with arms hanging towards the floor, then raises the dumbbell, thumbs pointing upwards, with a fully extended elbow using flexion of the shoulder in the sagittal plane to a 120° shoulder flexion, defined by when the participant can see their own elbow, and returns to the start position. A string will be attached in front of the participant to help participants as well as evaluators to ensure that the movement will be performed in the whole ROMCalf press will be tested using the same machine as for the leg press. The feet are placed so that when the participant’s knees are fully extended the legs are aligned with the applied force from the machine. The starting position will be with fully extended knees and the whole sole of the feet on the surface and the end position will be at full individual plantar flexion. The placement of the feet will be noted so that the pre- and post-intervention testing will be done in the same positionChest press will be tested with the handlebars placed at mid-sternum height and while the participant grips the handles with the elbows at 90° flexion at sternum height. The back should lie be firmly on the backrest and both feet on the floor. When the participant reaches full extension in the elbows, the end position of the movement will be considered reached

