### Statistics

The primary analyses will be an intention-to-treat analysis (including all participants randomized) in addition, a complete case population (participants with complete outcome measurements independent on adherence to intervention), and a per-protocol analysis (defined as at least 80% overall attendance rate as well as no exacerbations during the last 2 weeks prior to follow-up assessment) will be performed. Missing data will be imputed in the intention-to-treat analysis using multiple imputation assuming data is missing at random conditional on participant severity of disease and history of exacerbations. This is because severity of disease and history of exacerbations are known risk factors for future exacerbations and may affect adherence to the training protocol [28].

Mixed models will be used for analysis of data with individuals at level 1 and center at level 2. Estimates of effect sizes will be computed using Cohen’s *d* (*d* = difference in group means/error SD within). Calculated as the difference between predicted means from the final mixed-effects model for a given pair of groups divided by the estimated within-group error SD in the model with the estimated value of $$ 2{\sigma}_e^2 $$, where $$ {\sigma}_e^2 $$ is the residual variance. To judge the quality of the model we will analyze the residuals. For responsiveness, values of 0.20, 0.50 and ≥ 0.80 correspond to small, moderate and large responsiveness, respectively [50].

We will consider two-sided *p* values < 0.05 as statistically significant for the primary outcomes without correction for a multiplicity of tests assuming that each test represents an independent function based on the specificity principle of training [26]. Relationships between parameters will be evaluated using Pearson correlation coefficients. The strength of the correlation coefficients will be categorized as low (0–0.25), moderate (> 0.25–0.50), strong (> 0.50–0.75), very strong (> 0.75). Pre-planned subgroup analyses are differences between men and women. Statistical analysis will be performed using the statistical package SPSS 23.1.

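### The stated imputation of missing week-9 values leaves out the interim 1RM and multiple-RM results, which record how many drop-outs were responding to training

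*Protocol article*

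**What the plan says.** - **Primary measures.** The section on isotonic strength and endurance defines them as 1RM and an "endurance test (maximum number of repetitions performed at 45% of 1 RM"), each on four exercises. It adds: "The tests will be performed in order to individualize progression and to determine the effects of the training performed".
- **Interim tests.** Under Training interventions, training runs "three times per week for 8 weeks", and in both arms new 1RM and "multiple RM tests will be performed three times during the 8-week intervention period (after session 5, 10 and 15") are scheduled. Their stated purpose is "in order to optimize exercise loadings".
- **Outcome time points.** The section on screening tests and baseline characteristics states: "Primary and secondary outcome assessments will be conducted at two (three if accepting a biopsy) test occasions at weeks 0 and 9".
- **Analysis.** Under Statistics: "Mixed models will be used for analysis of data with individuals at level 1 and center at level 2". No level for repeated occasions is given. For the intention-to-treat analysis, missing data are multiply imputed as missing at random conditional on disease severity and exacerbation history. The reason given is that both predict exacerbations and may affect adherence.

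The article gives the interim results no role in the analysis or in the imputation.

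**The concern.** Missing at random is credible only if the imputation conditions on what drives missingness. The two named factors are known before training starts, and neither describes how the participant responded to it. In a training trial where participants know their programme, poor response or poor tolerance is a plausible reason to leave, and it could act differently under the two regimens. That is not established, but the protocol thinks drop-out worth comparing between regimens as a feasibility outcome.

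Adding arm and the baseline outcome to the imputation would not settle this. Someone who trains for 15 sessions without gaining and then leaves would still be given roughly the gain of a typical completer in that arm. At stake is the credibility of the primary intention-to-treat difference. Power is not the issue.

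**Working it through.** **1. The plan's own figure.** With a difference of 1.16, SD 1.09, two-sided alpha 0.05 and 80% power, the normal approximation gives 2 × (1.09 × (1.960 + 0.842) / 1.16)² = 13.86 per arm. Then 13.86 × 1.15 = 15.9, which is the stated 16 per group. (Dividing by 0.85 gives 16.3, so 17.) This point does not dispute that figure. Expected drop-outs among the planned 64 are 0.15 × 64 = 9.6.

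**2. How many drop-outs would have an interim result?** There are 3 × 8 = 24 sessions. The article gives no drop-out timing, so the timing is assumed.

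| Assumed timing | At least one interim result |
|---|---|
| Even, last completed session 1 to 23 | 19/23 = 83% |
| Even over 24 sessions | 19/24 = 79% (about 7.6 people) |
| Strongly front-loaded, F(t) = (t/24)^0.5 | 1 − (5/24)^0.5 = 54% |

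Under this form the share falls below half only if more than half of drop-outs leave within the first five sessions.

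**3. Bias without the interim results.** Suppose 15% drop out in each arm, and NLPRT drop-outs gain 1.16 less than NLPRT completers while RT drop-outs gain the same as RT completers. Arm-specific imputation that ignores interim results gives NLPRT drop-outs the completers' gain. The bias is 0.15 × 1.16 = 0.174.

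**4. Remaining bias with the interim results.** Assume a between-patient SD of gain of 1, test-error SD σ from 0.15 to 0.45, and even timing over sessions 1 to 23. If a fraction f of the final gain is present at a test, the readings available recover a share R = Σf² / (Σf² + σ²) of a drop-out's deficit. The remaining bias is 0.174 × (1 − average R).

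*Linear gain.* Here f = 5/24, 10/24 and 15/24, so Σf² = 0.043, 0.217 and 0.608 for one, two and three readings. The shares of drop-outs with exactly none, one, two and three readings are 4/23, 5/23, 5/23 and 9/23.
- σ = 0.15: R = 0.66, 0.91, 0.96; average 0.717; remaining bias 0.174 × 0.283 = 0.05.
- σ = 0.45: R = 0.18, 0.52, 0.75; average 0.444; remaining bias 0.174 × 0.556 = 0.10.

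*Late gain.* The NLPRT section puts more emphasis on strength in the first four weeks and on endurance in the last four. As the extreme case, let endurance gain begin only after session 12. Only the session-15 test is then informative, with f = 3/12 = 0.25 and f² = 0.0625.
- σ = 0.15: R = 0.0625/0.085 = 0.735; average 9/23 × 0.735 = 0.288; remaining bias 0.174 × 0.712 = 0.12.
- σ = 0.45: R = 0.0625/0.265 = 0.236; average 0.092; remaining bias 0.174 × 0.908 = 0.16.

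**5. A different mechanism.** Let poor interim response drive drop-out directly, in one arm only, with 15% drop-out and an interim-to-week-9 correlation of 0.5 to 0.85. In a large-sample simulation the true difference of about 1.06 SD (1.16/1.09) is estimated as 1.15–1.22 when interim results are ignored and as 1.08–1.10 when they are used. With the same mechanism in both arms there is no bias either way.

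**6. Precision when drop-out is unrelated to response.** In a simulation with 32 per arm, using the interim results reduces the error from missing values and test noise from 0.114 to 0.068 (σ = 0.15) or from 0.163 to 0.151 (σ = 0.45). Patient sampling error, √(2/32) = 0.25, must be added.
- √(0.25² + 0.114²) = 0.275 against √(0.25² + 0.068²) = 0.259: 6% lower.
- √(0.25² + 0.163²) = 0.298 against √(0.25² + 0.151²) = 0.292: 2% lower.

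**The case against.** The strongest reply is that a pre-post analysis with multiple imputation is legitimate, that auxiliary variables are usually settled in the analysis plan, and that the article does not say no other variable may enter. The first part stands: nothing here is a contradiction. The rest stands only in part. The article states the missing-at-random assumption together with its conditioning set and a reason for it, so the comment addresses a stated choice and not an absent detail.

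Four further objections hold and limit the point.
- **The bias is conditional.** It needs drop-out that depends on response and differs between arms. The only driver of non-adherence the article names is exacerbation. Stopping training also need not mean a missing week-9 test, because the complete-case population is defined regardless of adherence.
- **Linear gain is the favourable case.** The 1.16 advantage is hypothesised for endurance, while strength effects are expected to be similar. Endurance is also what NLPRT emphasises late, so early tests may predict it weakly.
- **Interim values are not equivalent to the masked assessments.** They come from a programme whose instructors are unmasked and serve to set loads. A 1RM below the previous one triggers a retest and the higher training load is kept. That rule acts on poor responders and could push their record upward; the calculation treats interim error as unbiased.
- **The precision gain is small.** A reader might look only at the error from missing values and test noise and infer a reduction of up to 40% (0.114 to 0.068). Once sampling error is counted, this is 2–6%.

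**Conclusion.** The point holds as an inexpensive improvement to a stated method. The imputation names two pre-training factors although direct measurements of training response are scheduled in both arms. In the illustrative one-sided case the bias of about 0.17 falls to 0.05–0.10 under linear gain, and to about 0.12–0.16 if endurance gain comes late; the truth probably lies between. These figures rest on 15% missing per arm, a 1.16 deficit in NLPRT drop-outs only, even drop-out timing, and unbiased interim tests. With the same drop-out mechanism in both arms the bias is nil.

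Three stronger readings are tempting, and the documents do not support them:
- **That the primary result will be biased.** Nothing shows that response-driven drop-out will occur or will differ between arms.
- **That there are five interchangeable readings of each primary outcome, so a repeated-measures model should be primary.** Outcome assessment is fixed at "test occasions at weeks 0 and 9 (before and after intervention", and the interim tests are unmasked load-setting tests.
- **That most drop-outs would certainly have interim data.** This depends on timing the article does not give: about 80% if even, about 54% if strongly front-loaded.

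The stated sample size is unaffected.

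**What to change.** 1. Enter the session 5, 10 and 15 results in the trial database for each exercise, with test load, repetitions and a flag for any retest. Load is needed because a repetition count can be interpreted only at a known load.
2. Amend Statistics so that the imputation of week-9 1RM and multiple RM includes, by arm, the baseline value and the available interim values of the same exercise as auxiliary variables, alongside disease severity and exacerbation history.
3. State that the masked week-9 value is the only outcome. Any repeated-measures model that includes the interim values is a sensitivity analysis only.

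The cost is data entry for tests already scheduled and a short change of wording, with no extra visits or participants. The trial was still recruiting when the protocol was submitted, so the results could be captured prospectively. The downside is that interim values are noisier, come from an unmasked training setting and may be affected by the retest rule. They should therefore only help to predict missing week-9 values.

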
### NLPRT

The primary objectives of the NLPRT program will be to increase muscle strength as well as muscle endurance. The NLPRT program will be designed based on the structure shown in Fig. 3. The 8-week NLPRT program will target various aspects of limb-muscle function by alternating between the different intensity zones [24]. Number of sets, number of repetitions, intensities (% of 1 RM) and rest periods will be based on what is presented in Fig. 3.

**Fig. 3 Fig3:**
[figure not shown]
Structure for periodized resistance training [24]

Furthermore, the NLPRT program will be divided into three phases, a base phase (1 week), an intermediate phase (1 week) and an optimizing phase (6 weeks (of which 2 weeks are optimized for limb-muscle strength and 4 weeks optimized for limb-muscle endurance)). An overview of the pre-planned NLPRT setup, including information on how exercises will be progressed, is seen in Fig. 4. Within the NLPRT program, the first 4 weeks will focus more on muscle strength (exercise zones C and D) while the last 4 weeks will focus more on muscle endurance (exercise zones A and B). Progression of exercise will be symptom dependent and will be based on Borg CR10 exertion and fatigue ratings.

**Fig. 4 Fig4:**
[figure not shown]
Pre-planned setup of the non-linear periodized resistance training (NLPRT) and resistance training (RT) program. *For < 20 repetition sessions, adjustments will result in increases in intensity ranging between 2 and 10% [23]. †For ≥ 20 repetition sessions, adjustments will result in increases in volume (+ 10 repetitions for lower extremity exercise and + 5 repetitions for upper extremity exercises). §A fixed increase in load of 5% will be added if 12 repetitions are performed in all sets in 2 consecutive sessions [9, 26]

### RT

The primary objective of the RT group will be to increase muscular strength. The RT program will be performed in line with current guidelines, i.e., three sets of 8–12 repetitions at an initial load equal to 60% of 1RM (similar to zone C [Fig. 3]) [9, 25] that are recommended for increasing muscle strength in patients with COPD [9]. Rest between sets will be 2 min. Progression of exercises, fixed 5% increase in load, will be performance-based, i.e., an increase occurs when an individual can perform 12 repetitions on the current workload, on two consecutive training sessions [9, 26]. An overview of the pre-planned structure for the traditional resistance training group is seen in Fig. 4.

#### Adherence to intervention

To promote participant retention, efforts will be made to make training sessions in both groups enjoyable for participants. This will include easy access to the facility by the means of transportation preferred by the participants, small training groups in a comfortable setting using equipment suitable for this group of people, and personal monitoring from medically educated instructors. To promote the number of sessions attended during the intervention period, the intervention period can be extended by maximum 1 week due to missed sessions.

The adherence to the intervention will be documented by the instructor conducting the training sessions. In the case that a participant misses a training session without prior notice, the instructor will contact the participant by phone on the same day.

#### Participant safety

Reasons for immediately stopping an outcome tests or training session for people with COPD will include the following: (1) chest pain, (2) intolerable dyspnea, (3) leg cramps, (4) staggering, (5) diaphoresis and (6) pale or ashen appearance [27]. The assessors and instructors are trained to recognize these problems and to deliver the appropriate intervention. Further, this will be reported as an adverse event. If a participant experiences pain/discomfort from the exercising limb during training no progression will occur even if the participant reaches other requirements for progression in the NLPRT or RT group, respectively. If pain prohibits execution of an exercise, this specific exercise will be removed.

#### Data collection, management and analysis

The assessors will have previous experience of the included outcomes and formal training will be provided to the instructors of the training programs. If necessary, protocols for each measurement and exercise will be developed to assist instructors. These protocols will be available on request from the principal investigator.

##### Screening tests and baseline characteristics

A pulmonary function test (spirometry), while being on the participant’s usual bronchodilator therapy, will be obtained according to guidelines [28]. Anthropometrics will include height, weight and body mass index. To document baseline level of physical activity, participants will also be instructed to wear an accelerometer (DynaPort®, McRoberts BV, The Netherlands), placed on the lower back during seven consecutive days before the intervention period. The quantity of physical activity will be assessed using the median number of steps per day collected on at least two consecutive weekdays over at least 8 h of daytime [29]. Primary and secondary outcome assessments will be conducted at two (three if accepting a biopsy) test occasions at weeks 0 and 9 (before and after intervention). Before and directly after all physical tests, the perception of dyspnea and muscle fatigue will be measured with the Borg CR10 [23] as commonly and reliably used in patients with COPD [30–32].

